### 2.4. Intervention

The intervention started before the influenza season, running from October this year to February next year. Before the start of the influenza season, the eight communities were randomly allocated into four study arms: (1) IMB-based behavioral intervention, (2) conditional economic incentives, (3) a combination of IMB-based behavioral intervention and conditional economic incentives, and (4) the control group with usual care, with stratification by urban and rural areas.

**IMB-based behavioral intervention.** The older adults will receive behavioral intervention based on the IMB model (Figure 2). The underlying idea of the intervention is that vaccination behavior is closely related to the older adults’ vaccine knowledge, their motivation to reduce the risk of influenza infection through vaccination, and vaccination-related behavioral skills. The IMB model includes the following components: (a) information, comprising objective and subjective vaccine information; (b) motivation, including perceived susceptibility, attitudes (towards vaccines), and complying with social norms (e.g., peer recognition of vaccine); and (c) behavioral skills, mainly encompassing vaccine-related self-efficacy (e.g., managing side effects), action planning (scheduling vaccinations), and coping planning (dealing with vaccination obstacles) [33]. The conditional economic incentives could lead to behavior change via potential pathways, involving modulating the price effect, enhancing the income effect, and mitigating high discounting or present bias [34].

The main components of the intervention, designed based on the IMB model, will be implemented offline and include the following:

(a) Distribution of health education brochures. The printed health education brochures summarizing official information on influenza vaccination from WHO and China’s National Health Commission will be distributed once after the baseline.

(b) Lectures on influenza vaccination. Influenza vaccination experts will lead the lectures. Topics will cover information about influenza vaccine, improving intentions for influenza vaccination uptake, social norms for vaccination, self-efficacy in vaccination and managing potential side effects, and creating effective action plans for vaccine appointments. The research team will provide lecture materials. This component will also take place once.

(c) Interactive quizzes on influenza knowledge with prizes. Participants will engage in quizzes on influenza knowledge, using questions sourced from official core information. This activity will occur once.

(d) One-on-one consultations with doctors. Participants will have access to one-on-one consultations with doctors during the intervention period.

The intervention program will be implemented after the baseline assessment. The interventions will start at the beginning of the flu season and last for about one month. Supported by the research team, the community staff will be responsible for delivering the intervention and monitoring the process.

**Conditional economic incentives.** Two incentive conditions have been established: one is based on the timing of vaccination within the flu season, and the other is based on the number of people vaccinated together. First, each participant vaccinated within the first month of the flu season receives CNY 30 (or about USD 4.25 at current rates) as the early-bird incentive. The incentive is CNY 15 if the individual gets vaccinated within the second month and CNY 0 after the second month. Second, each participant receives CNY 30 if three or more people within the same household are vaccinated on the same day, while it is CNY 15 for two people and CNY 0 for one person vaccinated alone. The above two conditional incentives can be combined, offering a maximum total incentive of CNY 60 per person, which amounts to approximately 50% of the current market price for the influenza vaccination in 2024, set at CNY 114. Participants will be informed of the incentive system upon entering this study. The incentives will be delivered in cash after the verification of vaccination records.

**A combination of IMB-based behavioral intervention and conditional economic incentives.** Participants will receive both the IMB-based behavioral intervention and the conditional economic incentives during the intervention.

**Control arm: usual care.** Participants will receive usual care without additional interventions. This includes access to routine healthcare services, general health information available within the community, and informational posters in public spaces to promote influenza vaccination among all community members.

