### 2.5. Measurements

Participants will receive information about the study purpose, content, and procedures and sign a written informed consent form before the baseline assessment. Our research team independently developed the questionnaire regarding the scales used in the existing literature. The questionnaire includes the five main aspects: socio-demographic characteristics, vaccination intentions and status, vaccine literacy, and IMB-based vaccine cognization. A panel of specialists in epidemiology, psychology, and behavioral science will be invited to review and evaluate the face validity of the questionnaire and make the modification suggestions. The questionnaire will be tested on about 20 participants before formal use. Participants who complete the baseline and follow-up questionnaires will receive CNY 20 (≈USD 2.7) each time as compensation for their time.

**Sociodemographic characteristics:** Sociodemographic information will be collected, including gender, age, ethnicity, education level, occupation before retirement, place of residence, health status (including the presence of any chronic illnesses), personal monthly income, and insurance coverage status.

**Influenza vaccination intentions and status:** The vaccination intentions will be measured through questions assessing the participants’ willingness to receive the influenza vaccine in the current year. A five-point Likert scale ranging from “1 = strongly disagree” to “5 = strongly agree” will be used to capture their intention levels [35]. We will investigate the detailed information on the participants’ previous influenza vaccination experiences, encompassing their vaccination history in the last influenza season (from September 2023 to February 2024), the mode of payment for the vaccination, the accompanying individuals during the vaccination process, and any reasons cited for not being vaccinated. Information on pneumococcal vaccination status will also be collected.

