**IMB-based vaccination cognitions:** To develop these vaccination-related cognition measurements, we first conducted a thorough literature review of existing surveys and measures related to vaccination cognitions, particularly those guided by IMB theory or similar constructs including information (knowledge), motivation (positive attitudes) and behavioral skills (perceived behavioral control, capability). Then, we formed an item pool and critically reviewed by a multidisciplinary team to ensure its relevance and clarity [39,40]. For the IMB-based vaccine cognition section, we surveyed the following aspects using a Likert five-point scale, ranging from 1 (strongly disagree) to 5 (strongly agree): perceived susceptibility of influenza (e.g., “contracting influenza will impact my physical health”), attitudes towards vaccines (e.g., “influenza vaccination can prevent me from getting influenza”), the intention of influenza vaccination (e.g., “I will get the vaccinated this flu season”), social norms (e.g., “family, friends, or peers suggested that I get the influenza vaccine”), vaccine-related self-efficacy (e.g., “I know how to manage the side effects after receiving the vaccine”), action planning (e.g., “I can find out the time and location for influenza vaccination”), and coping planning (e.g., “I am aware of the procedure of influenza vaccination”).

The follow-up survey will be conducted during the final month of the influenza season, which is February of the following year. This follow-up will encompass two key components: a questionnaire survey (identical to the baseline questionnaire) and vaccination status verification through official vaccination records maintained by healthcare providers at community health service centers.

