### 2.6. Outcomes

The primary outcome is the influenza vaccination rate. The vaccination records will be collected from the collaborating health service center databases. This study does not provide free vaccination; participants need to pay for vaccination at the market price. The secondary outcome is the intention of influenza vaccination (under the free and paid scenarios), primarily from questions in the follow-up questionnaires.

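### In the two incentive arms, baseline intention may be recorded after participants hear of the cash offer, so it is not a safe pre-intervention value

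*Protocol article*

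**What the plan says.** The relevant statements are spread over four sections of the protocol article.

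- **Disclosure of the offer (Section 2.4, paragraph on conditional economic incentives):** "Participants will be informed of the incentive system upon entering this study". The cash itself is paid later, once vaccination records have been verified.
- **Information and consent (Section 2.5):** "Participants will receive information about the study purpose, content, and procedures and sign a written informed consent form before the baseline assessment".
- **Start of intervention (Section 2.4, after the list of IMB components):** "The intervention program will be implemented after the baseline assessment". The IMB brochures are separately stated to be handed out after baseline.
- **Allocation (Section 2.4):** "Before the start of the influenza season, the eight communities were randomly allocated into four study arms". Its order relative to enrolment of individuals is not given.
- **What baseline asks (Section 2.5):** "The vaccination intentions will be measured through questions assessing the participants’ willingness to receive the influenza vaccine in the current year". The February questionnaire repeats the baseline one.
- **Outcomes and analysis (Sections 2.6 and 2.7):** Intention is the only named secondary outcome and is taken mainly from the follow-up questionnaires. Difference-in-differences is specified for vaccine uptake. Mixed models are named for primary and secondary outcomes. Baseline intention and IMB scores are to be tested for balance between intervention and control.

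**The concern.** Until a participant is vaccinated and paid, a conditional incentive consists of knowing the offer, so telling people about it begins the exposure. If that happens before the baseline questionnaire, the item on willingness to be vaccinated this year is answered with the offer already in mind in two arms. In the other two arms it is answered before any intervention.

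Two uses of the baseline score would then mislead. A balance test could report an early treatment effect as chance imbalance. An analysis of intention that subtracts or adjusts for baseline would take out part of the effect it is meant to estimate. The behavioural arm would keep a clean baseline, so the incentive arms could look weaker beside it only because of the order of steps at the first visit. Once baseline has been collected in that order, the missing pre-exposure score cannot be recovered.

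**Working it through.** The plan gives no figure to reproduce here. The check is on the order of events, followed by algebra.

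**Order of events.** Sections 2.4 and 2.5 together suggest: entry and information (including the incentive rules), then consent, then baseline questionnaire. No sentence places disclosure of the rules after the questionnaire. For the IMB arm the order is explicit, with brochures and programme after baseline. If the sentence about implementation after baseline covers only the IMB components, the incentive arms have no such protection. If it covers all arms, it conflicts with disclosure on entry. Section 2.4 needs reconciling on either reading.

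**Number potentially exposed.** Two arms × 160 = 320 of 640.

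**Effect on an analysis of intention.** For an incentive arm against control, let *b* be the shift in mean intention at baseline caused by disclosure, and *f* the effect at follow-up. Then the expected contrast is:

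- follow-up only: *f*
- change from baseline or group-by-time: *f* − *b*
- adjusted for baseline with within-arm slope β (0 to 1): *f* − β*b*

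If the effect is stable at *d* and a share *c* of it is already present at baseline, then *f* = *d* and *b* = *cd*. The change contrast is *d*(1 − *c*) and the adjusted contrast is *d*(1 − β*c*). The documents give neither *d*, *c* nor β. For illustration only, take *d* = 0.30 points on the five-point scale and β = 0.5:

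| *c* | Follow-up only | Change from baseline | Loss | Baseline-adjusted (β = 0.5) |
|---|---|---|---|---|
| 0 | 0.30 | 0.300 | 0% | 0.3000 |
| 0.25 | 0.30 | 0.225 | 25% | 0.2625 |
| 0.5 | 0.30 | 0.150 | 50% | 0.2250 |
| 0.75 | 0.30 | 0.075 | 75% | 0.1875 |
| 1 | 0.30 | 0.000 | 100% | 0.1500 |

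The percentage loss in the change contrast equals *c* whatever *d* is. The 0% to 100% range assumes that the effect has not faded by follow-up. If it has (*f* < *b*), the change contrast turns negative. Section 2.4 ends the timing payment after the second month and Section 2.5 places the follow-up survey in February, so fading is conceivable, but nothing in the article establishes it.

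**Contrasts not affected.** For the behavioural arm against control, *b* = 0. For the combined arm against incentives alone, the shift cancels if disclosure acts equally in both. For uptake, Section 2.5 collects vaccination history for September 2023 to February 2024. Used as the pre-value, that status predates disclosure and cannot be altered by it.

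**The case against.** A reader might infer that the trial's difference-in-differences estimate is biased. The documents do not support that. The abstract and Section 2.7 attach difference-in-differences to vaccine uptake, which comes from records, and no sentence prescribes it for intention or any IMB score. Section 2.6 takes intention mainly from follow-up, and Section 2.7 does not say how the mixed linear model treats baseline, a detail that an analysis plan commonly settles. A follow-up-only model would lose nothing. This objection stands in full and limits the point to baseline comparisons and to analyses of intention that use baseline.

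The order is also inferred. Entering the study is not defined relative to the questionnaire, the information given before consent is described only in general terms, and the sentence about implementation after baseline may cover every arm. The order of steps within a visit may also be set out in the implementation manuals mentioned in Section 2.9. It is fair to call the order a strong inference rather than a stated fact. It is not fair to set the point aside, because the one sentence on timing of disclosure points to entry.

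Finally, it would be too much to say that all 320 participants are affected or that every IMB score shifts. The article gives no reason why a cash offer should move items on susceptibility or on handling side effects. Intention, above all under the paid scenario, is the likely candidate.

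**Conclusion.** The concern holds in a limited form. As written, baseline intention in the incentive and combined arms may be a post-exposure value for up to 320 of 640 participants, while it is a pre-intervention value in the other two arms.

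Two things follow. The planned balance tests of intention and IMB scores could show a treatment effect as imbalance, whichever outcome model is used. Any change-from-baseline, group-by-time or baseline-adjusted analysis of intention would lose some or all of the incentive effect already present at baseline. With a stable effect the loss is between 0% and 100%, and the article offers no basis for choosing a value within that range.

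The primary outcome is not biased by this route, provided its pre-value is prior-season status. The conclusion rests on reading study entry as coming before the questionnaire and on arm allocation being known at that time. It concerns the only named secondary outcome and the validity of baseline comparisons. That is enough to justify a cheap change before baseline data are collected.

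**What to change.** In Section 2.4, replace disclosure on entry with disclosure of the arm-specific incentive rules immediately after the baseline questionnaire, at the same visit and following general study consent. State there that the sentence on implementation after baseline applies to all intervention arms.

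The cost is a changed order of steps at that visit and ethics approval of the consent wording. The approval is a real condition, because Section 2.5 promises information on study content and procedures before consent. No extra visit or staff is needed.

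If disclosure must come before baseline, or already has, state that intention will be compared between arms at follow-up without the baseline intention score, and that baseline differences in intention will not be interpreted as imbalance. The cost of that route is the precision that a clean baseline score would have provided.

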### 2.5. Measurements

Participants will receive information about the study purpose, content, and procedures and sign a written informed consent form before the baseline assessment. Our research team independently developed the questionnaire regarding the scales used in the existing literature. The questionnaire includes the five main aspects: socio-demographic characteristics, vaccination intentions and status, vaccine literacy, and IMB-based vaccine cognization. A panel of specialists in epidemiology, psychology, and behavioral science will be invited to review and evaluate the face validity of the questionnaire and make the modification suggestions. The questionnaire will be tested on about 20 participants before formal use. Participants who complete the baseline and follow-up questionnaires will receive CNY 20 (≈USD 2.7) each time as compensation for their time.

**Sociodemographic characteristics:** Sociodemographic information will be collected, including gender, age, ethnicity, education level, occupation before retirement, place of residence, health status (including the presence of any chronic illnesses), personal monthly income, and insurance coverage status.

**Influenza vaccination intentions and status:** The vaccination intentions will be measured through questions assessing the participants’ willingness to receive the influenza vaccine in the current year. A five-point Likert scale ranging from “1 = strongly disagree” to “5 = strongly agree” will be used to capture their intention levels [35]. We will investigate the detailed information on the participants’ previous influenza vaccination experiences, encompassing their vaccination history in the last influenza season (from September 2023 to February 2024), the mode of payment for the vaccination, the accompanying individuals during the vaccination process, and any reasons cited for not being vaccinated. Information on pneumococcal vaccination status will also be collected.

**Influenza vaccine literacy:** Participants will answer questions about general vaccine literacy and influenza vaccine literacy. We will measure and evaluate both types of vaccine literacy through two dimensions: functional literacy and knowledge literacy. For the vaccine literacy measurements, the first draft was developed based on the World Health Organization (WHO) Vaccine Literacy Questionnaire, the Health Literacy Measurement Tool for Vaccines (HLS19-vac) and the China Influenza Vaccination Technical Guideline (2023–2024) [36,37,38]. Then the draft was reviewed by a multidisciplinary team to check for clarity and relevance to the Chinese context. The revised draft was finally pilot tested among 10 older individuals before its formal use.

For knowledge-based general vaccine literacy, we will investigate participants’ general knowledge about vaccines, such as their effects, side effects, and possible effects on the immune system. For functional general vaccine literacy, we will examine the behavioral ability of study participants to obtain information about vaccines, recognize the importance of vaccination, and determine the need for vaccination.

For the knowledge-based influenza vaccine literacy dimension, we will ask study participants about their knowledge of the benefits of influenza vaccination, physical reactions after vaccination, the relationship between the effectiveness of the influenza vaccine and influenza strains, and the preventive effects of the influenza vaccine. For functional influenza vaccine literacy, study participants will be asked about the recommended frequency of influenza vaccination, cost, perception of influenza prevalence, and ability to self-assess vaccination needs. We will also collect information on the perceived risks associated with influenza infections and the primary sources of vaccine-related details (e.g., healthcare providers, media, social networks) among participants.

**IMB-based vaccination cognitions:** To develop these vaccination-related cognition measurements, we first conducted a thorough literature review of existing surveys and measures related to vaccination cognitions, particularly those guided by IMB theory or similar constructs including information (knowledge), motivation (positive attitudes) and behavioral skills (perceived behavioral control, capability). Then, we formed an item pool and critically reviewed by a multidisciplinary team to ensure its relevance and clarity [39,40]. For the IMB-based vaccine cognition section, we surveyed the following aspects using a Likert five-point scale, ranging from 1 (strongly disagree) to 5 (strongly agree): perceived susceptibility of influenza (e.g., “contracting influenza will impact my physical health”), attitudes towards vaccines (e.g., “influenza vaccination can prevent me from getting influenza”), the intention of influenza vaccination (e.g., “I will get the vaccinated this flu season”), social norms (e.g., “family, friends, or peers suggested that I get the influenza vaccine”), vaccine-related self-efficacy (e.g., “I know how to manage the side effects after receiving the vaccine”), action planning (e.g., “I can find out the time and location for influenza vaccination”), and coping planning (e.g., “I am aware of the procedure of influenza vaccination”).

The follow-up survey will be conducted during the final month of the influenza season, which is February of the following year. This follow-up will encompass two key components: a questionnaire survey (identical to the baseline questionnaire) and vaccination status verification through official vaccination records maintained by healthcare providers at community health service centers.

### 2.6. Outcomes

The primary outcome is the influenza vaccination rate. The vaccination records will be collected from the collaborating health service center databases. This study does not provide free vaccination; participants need to pay for vaccination at the market price. The secondary outcome is the intention of influenza vaccination (under the free and paid scenarios), primarily from questions in the follow-up questionnaires.

### 2.7. Data Analysis

The mean and standard deviation will be used to describe the data for numerical variables such as intention to be vaccinated and scores on each element of the IMB model. The *t*-test will be used to compare the balance of baseline data between the intervention group and the control group for these variables. For categorical variables such as influenza vaccination, the rate will be used to describe the data, and the chi-square test will be used to compare the balance of baseline data between the intervention group and the control group.

We will estimate the Difference in Differences (DIDs) (with a 95% confidence interval (CI)) of the proportion of vaccine uptake between each intervention and control (non-intervention) arm, adjusting for the clustering effect and testing whether it is statistically significant or not at a 5% level of significance. This study will use mixed-effects models to evaluate the impact of the primary and secondary outcome indicators. A generalized mixed linear model will be used to assess the impact of categorical outcome variables, and a mixed linear model will be used to evaluate the effect of continuous outcome variables. The effect evaluation process will follow the intention-to-treat principle. All statistical analyses will be performed using IBM SPSS Statistics (version 27) and SAS (University Edition, version 9.4). The statistical significance level will be *p* < 0.05.

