## 2. Materials and Methods

### 2.1. Study Design

This study will use a cluster randomized controlled trial design, with the community as the unit of randomization and various interventions, to evaluate the effectiveness of IMB-based behavioral intervention and conditional economic incentives among the Chinese older adults. The primary outcome is influenza vaccination over the follow-up durations.

We will choose communities from different provinces where the influenza vaccine is not covered by the present health system and older adults needs to pay out of pocket. In the two targeted provinces (Jiangsu and Shandong), four communities will be selected from urban and rural areas within each province, resulting in eight communities in total. These eight communities will be stratified based on their urban or rural status and then randomly allocated to (1) the IMB-based behavioral intervention group, (2) the conditional economic incentives group, (3) the combined IMB-based behavioral intervention and conditional economic incentives group, and (4) the control group. We will assess influenza vaccine uptake before and after the intervention and between different study arms. Figure 1 illustrates the study design.

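### The primary difference-in-differences has no pre-period value defined from the outcome's own records, and under a logit link the named model would not estimate it directly

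*Protocol article*

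**What the plan says.** All references are to the protocol article.

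- **Effect measure.** Section 2.7 takes the DiD "of the proportion of vaccine uptake between each intervention and control (non-intervention) arm", with a 95% confidence interval and adjustment for clustering. The abstract also names DiD estimates.
- **Model.** The same section states: "A generalized mixed linear model will be used to assess the impact of categorical outcome variables". It names no link function.
- **Pre and post.** Section 2.1 promises: "We will assess influenza vaccine uptake before and after the intervention and between different study arms". It does not say where the earlier value comes from, and it defines the primary outcome as vaccination during follow-up.
- **Earlier vaccination status.** Section 2.5 lists, among the questionnaire items, "their vaccination history in the last influenza season (from September 2023 to February 2024").
- **Later vaccination status.** Section 2.5 makes "vaccination status verification through official vaccination records maintained by healthcare providers at community health service centers" a component of the February follow-up. Section 2.6 adds: "The vaccination records will be collected from the collaborating health service center databases". It names no season. The Discussion says that official records are used in place of self-report for the primary outcome.
- **Season.** Section 2.4 describes it as "running from October this year to February next year".

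**The concern.** A DiD of proportions needs two values per arm, measured in the same way. The plan describes the later one as record-based. The only earlier one it describes is a questionnaire answer, for a window that opens a month sooner. If the analysis uses that answer, error in recalling last season's vaccination goes straight into the primary effect, together with ordinary between-season variation. Misreporting could well differ between arms. Each arm is only two communities, so community differences average out poorly. Section 2.4 also places allocation before the season and has participants told about the incentive scheme on entry, so knowledge of the arm could colour the answers.

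The second issue is scale. The effect is promised as a difference in proportions, while binary outcomes go to a generalized mixed model. With the customary logit link, the arm-by-time coefficient is on a different scale, and its sign need not match. The Introduction gives uptake of 0.5% to 5% in regions without free vaccination, which is where this trial recruits. At such rates a baseline arm may hold no vaccinated participant at all.

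**Working it through.** **Inputs from the article.** 160 participants per arm, four arms, planning rates 8% and 16% (section 2.3); uptake 0.5% to 5% without free vaccination (Introduction). **Assumed, not in the article:** the link function, the accuracy of self-report, and the within-person correlation r between seasons. The article gives no DiD figure to reproduce.

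**1. Misreporting, if the questionnaire supplies the earlier value.** Reported rate = p·Se + (1−p)(1−Sp), with true baseline p = 8% in both arms, follow-up 8% (control) and 16% (intervention), so the true DiD is +8 points.
- Same Se and Sp in both arms: the reported baselines are equal and cancel. The DiD stays at +8 points.
- Se 0.95 in both; Sp 0.98 in control, 0.90 in intervention: reported baselines are 0.076 + 0.0184 = 9.4% and 0.076 + 0.092 = 16.8%. The DiD is 8 − 7.4 = +0.6 points.
- As above, with Sp 0.88 in intervention: reported baseline 18.6%. The DiD is 8 − 9.2 = −1.2 points.

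**2. Scale, if the link is logit.** Ratio of odds ratios = exp{[logit(post) − logit(pre)] in intervention − the same in control}.
- Control 2% to 4%, intervention 6% to 10%: DiD = 4 − 2 = +2 points. The odds ratios are 0.1111/0.0638 = 1.741 and 0.0417/0.0204 = 2.042; their ratio is 0.85.
- Equal baselines, control 8% to 8%, intervention 8% to 16%: DiD +8 points, ratio 2.19. The signs agree.

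**3. Empty baseline arms.** The chance that one arm has none vaccinated is q = (1−p)^160; for at least one of four arms it is 1 − (1−q)^4, treating participants as independent.

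| Baseline uptake p | At least one arm with none vaccinated |
|---|---|
| 0.5% | 91% |
| 1% | 59% |
| 2% | 15% |
| 5% | 0.1% |
| 8% | below 0.001% |

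**4. Precision of DiD against adjusting for baseline.** Let vb = 0.08 × 0.92 = 0.0736 and v1 = 0.16 × 0.84 = 0.1344. The DiD variance is proportional to 2vb(1−r) + vb + v1 − 2r√(vb·v1), and that of unadjusted follow-up to vb + v1. Adjustment uses one common baseline slope. Cluster effects are ignored.

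| r | DiD variance (unadjusted = 1) | Adjusted variance | SE ratio, DiD to adjusted |
|---|---|---|---|
| 0.3 | 1.21 | 0.91 | 1.15 |
| 0.5 | 0.88 | 0.76 | 1.08 |
| 0.7 | 0.54 | 0.52 | 1.02 |

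DiD equals unadjusted follow-up at r = vb/(vb + √(vb·v1)) = 0.0736/(0.0736 + 0.0995) ≈ 0.43. Below that it is the noisier of the two.

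**The case against.** A reader might infer that the plan subtracts self-report from records. It does not say so. Section 2.6 leaves the season of the records open, so the databases could supply last season too, and the Discussion's preference for records points that way. The questionnaire item sits among questions on payment, companions and reasons for not being vaccinated, and is never named as the pre-period value. This stands: what can be shown is that no record-based earlier value is described. The remaining candidate, current-season status at baseline, would be near zero by construction and leave the DiD with little purpose.

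A reader might also infer a logistic model. The text does not name one. An identity link, or standardisation after a logit fit, would give the promised difference in proportions, and an analysis plan that is not shown may settle the link. This stands too, so the scale argument is conditional.

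It is also fair that sign reversal needs unequal baselines, that misreporting common to all arms cancels when true baselines are equal (as would a shared window difference), and that empty arms are negligible at the 8% planning rate. DiD is valid under randomisation, and it removes stable community differences, which the precision table does not credit. The greater efficiency of adjustment does not make DiD an error.

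What the objection does not remove is the gap between the two measures as written, in a trial whose own figures for its setting put baseline uptake as low as 0.5%.

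**Conclusion.** The point holds in a limited form. The plan fixes a DiD of uptake proportions but describes no earlier value from the source that supplies the outcome. Followed as written, the two terms differ in source and by a month in window.

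The consequences are conditional. If the questionnaire is used and misreporting differs between arms, an 8-point effect could be largely cancelled; the specificities behind that example are assumed. If the link is logit, the model term can disagree in sign with the DiD when baselines are unequal, which is plausible with two communities per arm. It would often be inestimable at uptake near 1%, but not at 5% or above. The precision loss against adjustment is about 15%, 8% and 2% in standard error at r = 0.3, 0.5 and 0.7. It rests on an unstated correlation and a large-sample, individual-level argument, so it is secondary.

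The documents do not support saying that the primary effect is necessarily noisy or wrong-signed.

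**What to change.** 1. Extract each participant's 2023–24 vaccination status from the same centre databases, over the same calendar months as the trial season, and state that this is the baseline value. Reconcile the September and October season starts.
2. Make the primary analysis record-based follow-up uptake, with arm and urban/rural stratum as fixed effects, last-season uptake as a covariate and community as a random effect.
3. Report a standardised (marginal) risk difference with its 95% confidence interval, and state how it is derived from the model.
4. Keep the DiD of proportions, on the record-based baseline, as a sensitivity analysis.

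The cost is one more extraction from databases already being accessed, plus revised analysis wording. The drawback is that the DiD announced in the abstract becomes secondary. In return, the source mismatch goes, and an arm with nobody vaccinated last season no longer prevents estimation. The change does not address the small number of communities.
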